### Adverse events

The D-sorbitol and placebo solutions are considered safe for humans. In the case of an adverse event, the participant may be withdrawn from the study at the discretion of the attending physician. At that time, the participant will receive appropriate medical attention. Adverse events will be monitored and recorded one by one. The adverse event incidence rates will be calculated, but not aggregated or analyzed.

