### Participants

Patients attending or hospitalized at the Department of Psychiatry, Nagoya University Hospital, Nagoya, Japan, will be included in the study. The sample size was set as 20 by the following statistical calculation. Using the 7-point Likert scale, we defined 1 to 3 points as improved and 4 to 7 points as non-improved. The McNemar test was used to estimate the sample size for the improved/non-improved binary data. McNemar’s test was used to determine the number of cases required to obtain a significant difference (significance level: 5% two-sided) with more than 90% power in the crossover study. As a result, the number of cases to be analyzed was nine for each group (18 cases in total), assuming a dropout rate of 10%. To reach the target sample size, we will recruit through advertisements at Nagoya University Hospital.

The inclusion criteria are as follows: 1. Adult patients with schizophrenia or psychotic features based on the Diagnostic and Statistical Manual of Mental Disorders, 5th edition (DSM-5), regardless of gender; 2. Patients using sublingual asenapine tablets for more than 2 weeks; and 3. Patients who can provide written informed consent. The exclusion criteria are: 1. Patients with physical diseases or symptoms requiring medical treatment; 2. Pregnant and lactating women; 3. Patients with a history of convulsions; 4. Patients with a substance use disorder; 5. Patients with a taste disorder; 6. Patients with an olfactory disorder; 7. Patients who cannot understand the questionnaire protocol; and 8. Other patients whose inclusion in the study is deemed inappropriate by the attending physician. We will interview participants to determine if they meet these exclusion criteria. The reason for excluding olfactory disorder is that an associations between olfactory and bitter taste receptors has been suggested, and olfactory disorder may also affect the evaluation of taste [11]. The discontinuation criteria are: 1. If the research participant requests discontinuation; and 2. If the attending physician determines that there will be a clear disadvantage in the participant’s disease.

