### Study drug

Participants will receive D-sorbitol as the active drug and distilled water as the placebo. Participants will rinse with 25 mL of the study drug immediately before taking the sublingual asenapine tablet. Both D-sorbitol and distilled water will be kept clear and colorless to maintain blinding. During the study period, patients will be instructed to rinse their mouths by themselves at home or in the hospital ward. Afterwards, the patients will answer a multiple-choice questionnaire, which will be collected later.

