### Experimental schedule

The experimental schedule is shown in Table 1 and Fig. 1. The study will have two groups. Group A will receive D-sorbitol first (test period ① using D-sorbitol and test period ② using placebo solution), and Group B will receive the placebo solution first (test period ① using placebo solution and test period ② using D-sorbitol). There will be a 1-day interval between study periods ① and ②. The study will be conducted in the ward for inpatients and at home for outpatients at the same time of day as the administration of the sublingual asenapine tablets. The participants will provide the following information: disease onset category, duration of illness from the first onset, DSM-5 specific terms, total Positive and Negative Syndrome Scale score at enrollment, sublingual asenapine tablet starting date, asenapine dosage, concomitant medications, comorbidities, smoking history, height, and weight. Before the study, the participants will complete a multiple-choice questionnaire regarding the side effects and duration of getting used to asenapine. Also, after the study is completed, a questionnaire regarding the efficacy of the intervention will be administered.

**Table 1 Tab1:** Experimental schedule

	Experimental schedule				
	Baseline	Experimental period			Discontinuation
Day	Day 0	*Day 1*	*Day 2*	*Day 3*	
Participant background	○				
PANSS	○				
Height, weight	○				
Pre-questionnaire	○				
*Oral rinse with* *D**-sorbitol or placebo*		○		○	
*Post-implementation questionnaire*		○		○	
*Adverse events*					○

*PANSS* Positive and Negative Syndrome Scale

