### Ethics and dissemination

This study was registered in the Japan Registry of Clinical Trials (jRCTs041210019) on May 14, 2021. The study protocol was approved by the Nagoya University Clinical Research Review Board (CRB4180004). All methods will be carried out in accordance with the Declaration of Helsinki. Informed consent will be obtained from all study participants by the primary investigator or coinvestigators. For privacy protection, all participants will be identified using an anonymous identification code. The participants will be informed by the researcher about potential benefits, risks, alternatives, and responsibility during the study throughout the consent process. If any necessary experimental data are provided to a joint research institution, it will be carefully protected using only the participant’s identification code and a corresponding table. The acquisition of informed consent, the inclusion/exclusion criteria, participant eligibility, and the occurrence of any adverse events will be confirmed by an independent monitor from the research institution. The monitor will check whether the research procedure was carried out based on the approved procedure and confirm that the data storage method is appropriate. The findings from the research will be published in peer-reviewed journals and presented at local, national, and international conferences.

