## Discussion

This purpose of this study is to determine the efficacy of D-sorbitol in masking the bitter taste of asenapine. To our knowledge, this is the first intervention study with using D-sorbitol in patients with schizophrenia. There have been reports from asenapine clinical trials regarding the bitter taste of asenapine. The FDA has approved a black cherry-flavored sublingual tablet [12]. Although a registered randomized controlled trial compared raspberry-flavored with unflavored asenapine, its outcome has yet to be published [12, 13]. Even if this flavored formulation can reduce the bitterness of asenapine, it is still not available outside the United States. The clinical data show that the frequency of oral hypoesthesia with asenapine in Western populations may differ from that in Asian populations. For example, the incidence of oral hypoesthesia in Asian populations is about 10%, compared with only about 5% in Western populations [6, 13]. This gap may be the result of differences in the perceived intensity of the bitter taste among ethnic groups. Asians are far more sensitive to bitter tastes than are African-Americans, White people, and Hispanics [14].

Although D-sorbitol is more effective in masking bitterness in basic research, other substances, such as glycerin, propylene glycol, saccharin, and xylitol, can mask the bitter taste of asenapine [10]. However, D-sorbitol is inexpensive, available by prescription, and can be used without concerns about drug interactions or side effects, making it easy to put into practical use. It also offers significant advantages for patients who already comply with the administration procedure of sublingual asenapine tablets, such as the ability to alleviate side effects without changing drugs. If this trial can confirm the efficacy of D-sorbitol, pretreatment with D-sorbitol could provide an easy and inexpensive means of improving adherence.

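### Table 1 schedules adverse-event collection only at discontinuation, in conflict with the text, and the rule for reporting incidence rates contradicts itself

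*Protocol article*

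**What the plan says.** Four places in the protocol article bear on adverse events.

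- **Experimental schedule, Table 1.** The row labelled "Adverse events" carries a single mark, in the Discontinuation column. Days 0, 1, 2 and 3 are blank in that row. The rinse and the post-implementation questionnaire are both marked on Days 1 and 3.
- **Adverse events.** The text says "Adverse events will be monitored and recorded one by one". The reporting rule follows directly: "The adverse event incidence rates will be calculated, but not aggregated or analyzed".
- **Ethics and dissemination.** Among the monitoring duties, "the occurrence of any adverse events will be confirmed by an independent monitor from the research institution".
- **Study drug and Questionnaire survey content.** Participants rinse unsupervised, at home or on the ward. "Afterwards, the patients will answer a multiple-choice questionnaire, which will be collected later". The three post-rinse items cover the state of the mouth before rinsing, the change in bitterness, and how easy the taste is to continue with. The one adverse-event item is in the pre-questionnaire and concerns asenapine.

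**The concern.** Staff are given two different instructions. Someone working from the schedule would assess adverse events only when a participant discontinues. Someone working from the text would record every event in every participant.

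The reporting sentence adds a second difficulty. It calls for a rate and rules out aggregation in the same breath. It gives no denominator, and it does not say whether rates are to be shown separately for D-sorbitol and water.

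What is at stake is how complete and how readable the safety information will be. If the schedule governs in practice, events in completers reach the record only when someone volunteers them. If the reporting sentence is taken at its word, whatever is recorded stays as individual entries with no summary by solution. Neither affects the bitterness endpoint.

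**Working it through.** **1. Sample size.** The Participants section says "The sample size was set as 20 by the following statistical calculation", and gives 18 cases to be analysed (nine per group) with 10% dropout. Inflating for dropout:

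18 / (1 − 0.10) = 20.

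This reproduces the stated figure.

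**2. Who has a scheduled assessment under Table 1.** The table's columns are Day 0, Day 1, Day 2, Day 3 and Discontinuation. Read by column position, the adverse-event mark falls under Discontinuation only. Applying the planned dropout:

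- expected to discontinue: 0.10 × 20 = 2
- expected to complete, with no scheduled adverse-event assessment: 20 − 2 = 18, or 18/20 = 90%.

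This restates the planning assumption under one reading of the document. It does not estimate how many events would be missed.

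**3. Who is covered under the text.** The Adverse events section sets no restriction to discontinuers. The monitor's duty in Ethics and dissemination extends to any event. Under the text, all 20 are covered.

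The two sources therefore differ on about 18 of 20 participants.

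**4. Whether a described instrument closes the gap.**

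| Instrument | When | Asks about events after the rinse? |
|---|---|---|
| Pre-questionnaire, item 3 | Day 0 | No; events before and after starting asenapine |
| Post-implementation questionnaire, three items | Days 1 and 3 | No |
| End-of-study questionnaire | After completion | Described only as concerning efficacy of the intervention |

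The article sets out the pre- and post-rinse items, so for those two the absence can be read directly. The items of the end-of-study questionnaire are not listed.

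**5. Whether a recorded event could be tied to a solution.** Group A uses D-sorbitol in the first period and water in the second, and Group B the reverse. "There will be a 1-day interval between study periods ① and ②", so the rinses fall on Days 1 and 3. An event with an onset date can therefore be placed after the first or the second solution. The design permits a summary by solution; the document does not say that one will be made.

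**6. The reporting sentence.** An incidence rate is (participants with an event) / (participants at risk). Forming the numerator already pools participants. A rate that is calculated but not aggregated does not exist, so the sentence has to be replaced or explained.

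**The case against.** The strongest reply is that the text governs. Events are to be recorded individually, rates are to be calculated, a monitor confirms any event, and nothing restricts this to discontinuers. This stands. A reader might infer from Table 1 that the trial cannot report tolerability by solution in completers, but the documents do not support that: the text provides for recording, and dated events can be linked to a rinse day. Nor do they show that the post-rinse questionnaire is the sole contact with outpatients, since questionnaires are collected afterwards and another is given at the end.

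The table was read from PDF, and a mark spanning Days 1 to 3 could have been lost. This stands as a caveat. The other rows fall in sensible columns, which makes the reading plausible but not certain.

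The reporting sentence may simply mean description without a formal test, which would be reasonable with 20 participants. That is probably the intent, but the words do not say it.

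Finally, how events are elicited and tabulated is often left to the full protocol or analysis plan. That is fair for missing detail. It does not answer a schedule that disagrees with the text, or a sentence that contradicts itself.

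**Conclusion.** The point holds as an internal inconsistency of minor severity. Table 1 and the text disagree on when adverse events are collected, and the reporting rule cannot be carried out as written. If the schedule were followed, about 18 of 20 participants would have no scheduled assessment, and the post-rinse questionnaire would not fill the gap. That size rests on the 10% planned dropout and on the table having been extracted correctly.

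A reader might also set this against the Discussion's remark that D-sorbitol "can be used without concerns about drug interactions or side effects, making it easy to put into practical use" and conclude that the trial is claiming a safety result it cannot deliver. The document does not support that. The remark explains why D-sorbitol was chosen over other masking agents and is not offered as a finding of this trial, whose endpoints are bitterness and willingness to continue.

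**What to change.** 1. Check the adverse-event row against the published Table 1. If it reads as extracted, mark Days 1, 2 and 3 for all participants and keep the Discontinuation mark, so that the schedule agrees with the Adverse events and Ethics and dissemination sections.
2. Add one item to each post-rinse questionnaire asking whether anything untoward occurred after the rinse (yes/no, describe, when it began).
3. Replace the reporting sentence with, for example: *The number and percentage of participants with at least one adverse event will be tabulated by solution (D-sorbitol, water) among all participants who rinsed at least once, each counted under every solution used. Events will be assigned to the most recent rinse by date of onset. No formal test will be made.*

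The cost is a table correction, one questionnaire line and one descriptive table. The sample size and the McNemar analyses are unaffected.

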### Ethics and dissemination

This study was registered in the Japan Registry of Clinical Trials (jRCTs041210019) on May 14, 2021. The study protocol was approved by the Nagoya University Clinical Research Review Board (CRB4180004). All methods will be carried out in accordance with the Declaration of Helsinki. Informed consent will be obtained from all study participants by the primary investigator or coinvestigators. For privacy protection, all participants will be identified using an anonymous identification code. The participants will be informed by the researcher about potential benefits, risks, alternatives, and responsibility during the study throughout the consent process. If any necessary experimental data are provided to a joint research institution, it will be carefully protected using only the participant’s identification code and a corresponding table. The acquisition of informed consent, the inclusion/exclusion criteria, participant eligibility, and the occurrence of any adverse events will be confirmed by an independent monitor from the research institution. The monitor will check whether the research procedure was carried out based on the approved procedure and confirm that the data storage method is appropriate. The findings from the research will be published in peer-reviewed journals and presented at local, national, and international conferences.

### Consent to publish

Not applicable.

## Discussion

This purpose of this study is to determine the efficacy of D-sorbitol in masking the bitter taste of asenapine. To our knowledge, this is the first intervention study with using D-sorbitol in patients with schizophrenia. There have been reports from asenapine clinical trials regarding the bitter taste of asenapine. The FDA has approved a black cherry-flavored sublingual tablet [12]. Although a registered randomized controlled trial compared raspberry-flavored with unflavored asenapine, its outcome has yet to be published [12, 13]. Even if this flavored formulation can reduce the bitterness of asenapine, it is still not available outside the United States. The clinical data show that the frequency of oral hypoesthesia with asenapine in Western populations may differ from that in Asian populations. For example, the incidence of oral hypoesthesia in Asian populations is about 10%, compared with only about 5% in Western populations [6, 13]. This gap may be the result of differences in the perceived intensity of the bitter taste among ethnic groups. Asians are far more sensitive to bitter tastes than are African-Americans, White people, and Hispanics [14].

Although D-sorbitol is more effective in masking bitterness in basic research, other substances, such as glycerin, propylene glycol, saccharin, and xylitol, can mask the bitter taste of asenapine [10]. However, D-sorbitol is inexpensive, available by prescription, and can be used without concerns about drug interactions or side effects, making it easy to put into practical use. It also offers significant advantages for patients who already comply with the administration procedure of sublingual asenapine tablets, such as the ability to alleviate side effects without changing drugs. If this trial can confirm the efficacy of D-sorbitol, pretreatment with D-sorbitol could provide an easy and inexpensive means of improving adherence.

In 2019, the FDA approved an asenapine formulation that may improve adherence. However, other factors may affect adherence. There is concern that compliance will decline because of economic reasons, i.e., its high price [15–17]. The use of an asenapine transdermal patch may be complicated for some patients, and may lead to erythema at the application site as a distinctive side effect; this was reported in approximately 10% of cases compared with a placebo in a phase III trial [18]. Furthermore, the asenapine transdermal patch differs significantly from sublingual asenapine tablets in terms of having an immediate effect on agitation [19, 20]. However, there are still situations in which the use of sublingual tablets is appropriate [21], and more treatment options could be beneficial for shared decision-making between psychiatrists and patients.

This study has several limitations. Our investigation does not include participants who discontinued asenapine owing to bitter taste, hence the evaluation of D-sorbitol could change if the sample population changes. Another limitation is that this study does not evaluate oral hypoesthesia as a parameter because bitterness is the main target of evaluation. Inclusion of patients newly taking asenapine and evaluation of oral hypoesthesia are needed in future studies. If this study can clarify the effect of D-Sorbitol on the bitterness of asenapine, it will be helpful to both patients and doctors as one way to improve adherence to asenapine.

## Data Availability

Not applicable.

## Abbreviations

DSM-5: Diagnostic and Statistical Manual of Mental Disorders, 5th edition
FDA: Food and Drug Administration
PANSS: Positive and Negative Syndrome Scale
